## 8.2 Schedule of Assessments – further details

### a) Physical Examination

Including height, weight, lying and 5 minute standing blood pressure, ECOG performance status. Patient's blood pressure needs to be monitored weekly for the first 6 weeks of treatment of cediranib +/- gefitinib. Patients/carers will monitor the patient's blood pressure daily and record this in the patient diaries. CRFs should reflect an average of the patient-reported daily values. If a patient has BP  $\geq 150/100$  mmHg at Screening, a further reading should be taken at least 24 hours later to assess eligibility. In event of hypertension, refer to hypertension management plan, see [Section 7.4.1.4](#).

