## 2.6 Outcome variables

### 2.6.1 Efficacy

#### 2.6.1.1 Primary outcome variable

Progression free survival (PFS) defined as the time from the date of randomisation to the date of first progression or death due to any cause, whichever one comes first.

The progression definition will be based on modified RANO criteria (Wen 2010), such that progression will be defined as the earliest time that at least one of the following occurs:

*As assessed by site staff at clinical assessments:*

1. **Clinical deterioration** not attributable to other causes apart from the tumour (e.g seizures, medication adverse events, complications of therapy, cerebrovascular events, infection, and so on) or changes in dexamethasone dose.

Clinical deterioration will be defined as:

- Decline in Karnofsky performance status from 100 or 90 to 70 or less, or a decline of at least 20 from 80 or less, or a decline from any baseline to 50 or less, for at least 7 days

- Decline in ECOG performance status from 0 or 1 to 2 or 2 to 3

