| Inclusion/exclusion criteria            | X                                        |                       |                                   |                     |                     |                     |                     |                                   |                                                                                                                                       |                                                                                               |                                                                                           |                                                    |
| Physical Examination a       | X                                        | X                     | X                                 | X                   | X                   | X                   | X                   | X                                 |                                                                                                                                       | X                                                                                             | X                                                                                         |                                                    |
| Neurological Examination                | X                                        | X                     |                                   |                     | X                   |                     |                     | X                                 |                                                                                                                                       | X                                                                                             | X                                                                                         | X h                                     |

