| Pregnancy tests (females of child-bearing potential) e | X         |                     |        |        |        |        |        |        |                                                                                                                                      |                                                                                                  |                                                                                           |                                                    |
| MRI f                                                  | X         |                     |        |        |        |        |        | X      |                                                                                                                                      | X                                                                                                | X                                                                                         | X                                                  |
| Karnofsky Performance Status                                      | X         | X                   |        |        | X      |        |        | X      |                                                                                                                                      | X                                                                                                | X                                                                                         | X                                                  |
| Mini-mental status exam                                           | X         |                     |        |        |        |        |        | X      |                                                                                                                                      |                                                                                                  |                                                                                           |                                                    |

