#### **h) Follow up assessment schedule after discontinuation**

If a patient discontinues due to reasons other than progression, the patient will continue to be followed-up every 6 weeks until progression or death. If a patient discontinues due to progression, or has progressed after discontinuation, the patient will continue to be followed-up every 12 weeks for survival (via telephone call). All efforts should be made by the Site to contact the patient's GP to assess their condition, if a patient fails to attend a clinic or cannot be followed up at site. The trial will be registered with the NHS Information Centre in the event that any patients become Lost to Follow Up.

Neurological status assessments should be continued until neurological deterioration has been documented on 2 consecutive 6 weekly assessments. Dexamethasone dose per day should be collected until progression documented (as outlined in [section 2.6.1.1](#))

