### 13.1.2 Procedures for discontinuation from treatment

Patients who discontinue the trial treatment should always be asked about the reason(s) for their discontinuation and the presence of any adverse events. If possible, they should be seen and assessed by an investigator(s). The patient should return investigational products.

If all study treatment is stopped during the study, the Principal Investigator/Sub investigator will perform the best possible observation(s), test(s) and evaluation(s) as well as give appropriate treatment and all possible measures for the safety of the patient. In addition, they will record on the Case Report Form (CRF) the date of withdrawal, the reasons, and treatment at the time of withdrawal.

If only one study treatment is stopped during the study, the patient will continue with the trial assessments as before. Reasons for stopping the first drug must be recorded on the CRF. The discontinuation assessment is only to be carried out upon discontinuation of both trial drugs.

At withdrawal, all on-going SAEs must be followed until resolution, unless in the Investigator's opinion, the condition is unlikely to resolve due the patient's underlying disease.

All new AEs occurring for up to 30 days after the last dose of any study medication must be recorded in the CRF. Ongoing AEs thought to be caused by trial treatment will be followed up until resolution or death. All SAEs occurring up to 30 days after the last dose of any study medication must be followed until resolution.

Patients who are not receiving treatment, but are being followed up for tumour assessments should also be followed up for procedure related SAEs, these should be reported on an SAE report form (see [section 10.2.2](#) SAEs). AE collection beyond the 30 days post treatment is not required for patients who have progressed and are being followed up for survival only.

For patients who are withdrawn from study treatment for reasons other than disease progression every effort will be made to continue with collecting the trial MRI scans every 6 weeks. Follow up clinic assessments should be carried out every 6 weeks as detailed in [section 8](#).

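### An ECOG decline counts as progression for primary PFS, but no ECOG score is scheduled once a patient has stopped both drugs

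*Protocol*

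**What the plan says.** Protocol section 2.6.1.1 states that "progression will be defined as the earliest time that at least one of the following occurs". The first criterion is clinical deterioration assessed by site staff, and it has two bullets. One is a Karnofsky rule. It covers a fall from 100 or 90 to 70 or less, and continues "or a decline of at least 20 from 80 or less, or a decline from any baseline to 50 or less, for at least 7" (the unit of this duration is days). The other reads "Decline in ECOG performance status from 0 or 1 to 2 or 2 to 3" and carries no minimum duration.

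Section 8.1 has a row for "Karnofsky Performance Status" but none for ECOG. ECOG appears in the list of pre-randomisation evaluations (section 5.2) and otherwise only in note a) of section 8.2, which defines the physical examination as "Including height, weight, lying and 5 minute standing blood pressure, ECOG performance status". The "Physical Examination a" row is marked at screening, baseline, weeks 1 to 6, cycle starts and discontinuation. It is blank at mid-cycle visits and for Long term Follow Up.

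For a patient who stops treatment for a reason other than progression, section 8.2 h says "the patient will continue to be followed-up every 6 weeks until progression or death". Section 13.1.2 says "Follow up clinic assessments should be carried out every 6 weeks as detailed in" section 8.

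**The concern.** Patients who have stopped both drugs without progressing remain at risk of the primary event and remain in the intention-to-treat analysis (section 16.2). Their visits can still detect progression by Karnofsky, MRI and death, but the schedule does not ask for the ECOG score that one bullet of criterion 1 needs. A patient with the same decline would be an event while on treatment and might not be one after stopping.

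An event missed at its visit is dated later, or the patient is censored at last contact (section 16.3), so measured PFS lengthens. If stopping both drugs is more common in one arm, that arm gains apparent PFS for a reason unrelated to efficacy. Scans can be re-read centrally at the end of the trial, but an ECOG score that was never taken cannot be recovered.

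**Working it through.** **Schedule against endpoint.** What section 8.1 marks for each route to progression:

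| Route | On treatment, 6-weekly visit | Discontinuation visit | Long term Follow Up |
|---|---|---|---|
| MRI | yes | yes | yes |
| Karnofsky | yes | yes | yes |
| ECOG (within physical examination) | yes | yes | **no** |
| Death | yes | yes | yes |

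The gap opens only when both drugs are stopped. Section 13.1.2 keeps the assessments unchanged if one drug is stopped. Mid-cycle visits also lack ECOG, but in both arms alike.

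**How much of the lost route does Karnofsky cover?** The protocol gives no conversion between the scales. Reading the Appendix 5 descriptions side by side, Karnofsky 80 fits ECOG 1, 70 fits ECOG 2, and 50 or below roughly fits ECOG 3.

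- From 100 or 90 to 70 or less: an event on both scales.
- From 80 to 60 or less: an event on both scales.
- From 80 to 70 (ECOG 1 to 2): an ECOG event only, because the Karnofsky rule needs a fall of at least 20.
- From 70 to 50 or less (ECOG 2 to 3): an event on both scales.
- Any fall lasting under 7 days: possible on ECOG only.

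The residual gap is therefore mainly the 80-to-70 fall and short-lived declines.

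**The plan's own figure.** Section 16.1 gives 110 events for medians of 4 and 6 months, one-sided 10% error and about 80% power. By Schoenfeld's formula, 4(1.2816 + 0.8416)² / (ln 0.667)² = 18.03 / 0.1644 = 109.7, so 110 events. Power at 110 events is 80.1%. The figure reproduces, and this point does not change it.

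**Simple count.** The rates here are assumptions; only 56 per arm (112 / 2) comes from the protocol. Affected first events per arm = share stopping both drugs before progression × share of first events seen first on ECOG × 56.

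- Combination arm: 0.20 × 0.30 × 56 = 3.4.
- Control arm: 0.10 × 0.30 × 56 = 1.7.
- Difference: 1.7 of 110 planned events.
- Over stopping rates of 5–30% and ECOG-first shares of 10–40%: from 0.05 × 0.10 × 56 = 0.3 to 0.30 × 0.40 × 56 = 6.7 per arm.

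**Simulation under no treatment effect.** Assumptions: exponential PFS with median 4 months in both arms; both drugs stopped at a uniform time in the first 3 months; 10, 20 or 40% of later progressions first visible on ECOG; those events detected 6 or 12 weeks late; 20,000 patients per arm, Cox model. One-sided error at 110 events is Φ(−1.2816 − ln(HR) × √(110/4)). For HR 0.951 this is Φ(−1.2816 + 0.0502 × 5.244) = Φ(−1.018) = 15.4%.

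| Stop both drugs, control v combination | Apparent HR | One-sided error (planned 10%) |
|---|---|---|
| 10% v 20% | 0.981–0.999 | 10.1–11.9% |
| 10% v 30% | 0.958–0.997 | 10.3–14.5% |
| 15% v 43% | 0.951–0.995 | 10.5–15.4% |
| 20% v 20% | 0.989–1.008 | 9.3–11.1% |

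The simulated log hazard ratio has a standard error of about √(2/20,000) = 0.01, so the equal-stopping row is noise around 1.00, and HRs above about 0.99 cannot be told from no effect. The 43% is borrowed from the toxicity threshold in section 16.5 as an extreme. It is not a forecast of stopping.

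**The case against.** The strongest reply is that the route is not shown to be closed. The definition in section 2.6.1.1 is the same on and off treatment, criterion 1 is judged at clinical assessments rather than by a row in a table, and those assessments continue six-weekly. Section 13.1.1 says that patients stopped for the conditions it lists should continue trial assessments, and the follow-up CRF, which is not shown, may have an ECOG field. This stands in part. It is fair to say that ECOG is unscheduled, not that it can never be recorded. But the general wording in section 13.1.1 does not name ECOG, and the grid that specifies the visits leaves it out.

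Second, little is lost. Karnofsky and MRI continue, and criterion 1 excludes decline due to medication adverse events or dexamethasone changes, which would remove some isolated ECOG shifts soon after a toxicity stop. This stands, and it makes the assumed 30% ECOG-first share look generous.

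Third, a reader might infer that the more toxic arm necessarily loses more events, so that PFS is biased towards the combination. The protocol does not support that as a fact. Toxicity attributed to gefitinib is managed by interrupting, reducing or stopping gefitinib (section 7.4.2), and section 8.2 k has the patient continue the other drug, so ECOG would still be scored. Some rules do stop both drugs, including those for interstitial lung disease (section 13.1.1) and recurrent severe diarrhoea (Table 10), so a difference between arms is plausible. No arm-specific rate of stopping both drugs is given.

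**Conclusion.** The mismatch is real. A component of the primary endpoint is not scheduled for patients who are off both drugs and still being followed for progression, so its ascertainment depends on treatment status. The written definition itself does not change when treatment stops.

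The effect is probably small. With 10% v 20% stopping, the apparent null hazard ratio stays at 0.98 or closer to 1, and one-sided error at about 12% or less. Errors near 15% need the extreme stopping rates combined with 40% of events ECOG-first and a 12-week delay. With equal stopping there is no systematic bias. All of these sizes rest on stopping rates, ECOG-first shares and delays that the protocol does not give. The planned 110 events and 112 patients are unaffected. The case for acting is that the data cannot be recovered afterwards and the correction costs almost nothing.

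**What to change.** In section 8.1, give ECOG performance status its own row beside Karnofsky and mark it in the Long term Follow Up column for the six-weekly visits until progression. State in section 8.2 h that both scores are taken at those visits. Confirm that the follow-up CRF has the field. Sections 2.6.1.1, 8.1 and 8.2 then agree, on and off treatment, in both arms.

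The cost is one table row and one CRF field at a visit that already takes place and already scores Karnofsky. No extra visits, patients or events are needed. Basing criterion 1 on Karnofsky alone would also remove the mismatch, but it would change the primary endpoint, so adding the row is the lighter change.

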### b) Baseline measurements

Lab, TSH and ECG measurements should be retested at baseline **only** if the screening period is greater than 7 days. Labs and ECGs must be evaluated within 7 days prior to randomisation to confirm eligibility.

### c) Urinalysis tests

Urinalysis- if a patient has two consecutive one plus (+) urine proteinuria dipsticks measurements at baseline, please measure urine protein/creatinine ratio (UPC) or collect 24 hours urine for total protein. If the patient has a change of two plus (++) or greater from baseline on two consecutive proteinuria dipsticks, please measure urine protein/creatinine ratio or collect 24 hours urine for total protein. If 24 hours protein or UPC Ratio is classified as CTCAE grade 3 please refer to and follow guidance in [section 7.4.1.1](#), management of proteinuria.

### d) Quality of life questionnaire timing

EORTC QLQ-C30 and BN-20 questionnaires should be completed before the patient receives any treatment and before given the results of their tumour assessments.

### e) Pregnancy test

Women of child-bearing potential (see [section 5.1.3](#)) must have a negative urine or serum pregnancy test at the screening visit within 14 days prior to starting trial treatment.

### f) MRI timing and guidance

Baseline contrast enhanced MRI must be completed within 7 days prior to randomisation according to acquisition guidelines. Follow-up scans should be performed at scheduled time points  $\pm 10$  days (every 6 weeks from the baseline date), independent of when the follow up assessment was completed or trial treatment administered. For acquisition guidelines see [Section 7.7](#) (Imaging).

Patients must be on a stable dose of steroids (dexamethasone) for at least 5 days prior to baseline scan and at least 10 days prior to all follow-up scans. At discontinuation the MRI should be performed within 10 days of discontinuation where possible.

For patients who are withdrawn from study treatment for reasons other than disease progression every effort will be made to continue with collecting the trial MRI scans every 6 weeks.

#### **g) Adverse event collection duration**

Adverse events will be collected from the time informed consent is given, throughout the treatment period and up to and including the 30 days after last dose of study medication. AEs thought to be related to trial treatment will be followed up until resolution or death. Any ongoing SAE at discontinuation must be monitored until resolution. SAEs occurring after 30 days following the last dose of study drug do not need to be reported to UCL CTC unless thought to be related to the study treatment.

#### **h) Follow up assessment schedule after discontinuation**

If a patient discontinues due to reasons other than progression, the patient will continue to be followed-up every 6 weeks until progression or death. If a patient discontinues due to progression, or has progressed after discontinuation, the patient will continue to be followed-up every 12 weeks for survival (via telephone call). All efforts should be made by the Site to contact the patient's GP to assess their condition, if a patient fails to attend a clinic or cannot be followed up at site. The trial will be registered with the NHS Information Centre in the event that any patients become Lost to Follow Up.

Neurological status assessments should be continued until neurological deterioration has been documented on 2 consecutive 6 weekly assessments. Dexamethasone dose per day should be collected until progression documented (as outlined in [section 2.6.1.1](#))

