## 2. Failure to return for evaluation as a result of death or deteriorating condition

In this instance, the earliest known date of death or deterioration will be used as the date of progression. Where unknown, the clinical assessment date at which the patient did not attend will be used (only for patients known to have not returned for evaluation due to death or deteriorating condition).

*As determined by retrospective radiographic central review:*

3. **Any new lesion** (short axis must be  $\geq 10$  mm on at least 2 axial slices that are 5mm apart with 0mm skip and the new lesion should be outside the original tumour volume)
4. **Increase in  $\geq 25\%$  of sum of the products of perpendicular diameters of enhancing lesions compared with baseline scan, on stable or increasing doses of steroids (dexamethasone) compared to baseline (T1 post-contrast scan)**
5. **Clear progression of non-measurable disease** (clinically significant increase in size with a short axis  $\geq 10$ mm on at least 2 axial slices that are 5mm apart with 0mm skip)
6. **Significant increase in T2/FLAIR non-enhancing lesion – on stable or increasing steroids (dexamethasone) compared with baseline or best response not caused by co-morbid events.** Precise quantification of the increase in T2/FLAIR signal can be difficult and must be differentiated from other causes of increased T2 or FLAIR signal, such as radiation effects, decreased corticosteroid dosing, demyelination, ischemic injury, infection, seizures, postoperative changes, or other treatment effects before making a determination of progressive disease. Changes in T2/FLAIR signal that suggest infiltrating tumour include mass effect (as determined by sulcal effacement, ventricular compression, and thickening of the corpus callosum), infiltration of the cortical ribbon, and location outside of the radiation field. The initiation of these changes can be subtle, and convincing non-contrast-enhancing growth may require one or two confirmatory scans. If non-enhancing progression is determined after retrospective review of images, the scan at which these changes were first detected should serve as the progression scan.

Examples of progression on T2/FLAIR:

- a. Substantial change in size of tumour with clear margins on T2/FLAIR
- b. New lesion(s) ( $\geq 10$ mm) which is completely distinct from original enhancing volume on T2 ( $\geq 50$ mm distance)

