**Table 11. Required MRI acquisition parameters**

Post contrast images must be taken in the order stated above. Measurements for all scans on MRI will be in the plane where the tumour is largest. All images are required for the trial. The critical scans are FLAIR, T2, post-contrast T1.

If additional scans are performed according to local guidelines, these should be submitted for the trial central review in addition to the trial images.

Images should be reported locally for the follow up CRFs. Images should be sent to UCL CTC in DICOM format on CDs as soon as possible after acquisition (ideally also with a DICOM reader), along with a completed Acquisition report (see Appendix 8) and local imaging report (where available). Images should contain a reference to the date of the scan. Images must have patient names removed, and refer to patients via study number (in addition, initials, NHS number and date of birth are permitted but discouraged). The central review of MRI scans will be carried out retrospectively at the end of the trial. If there are problems accessing scan images during the review, sites may be contacted again to create a new CD.

Locally reported radiological response should be reported as defined in 16.4, with progression as defined in 2.6.1.1. Please note that there is a high possibility of pseudoresponse and pseudoprogression on MRI scans in patients receiving angiogenesis inhibitors. Where treatment decisions are based upon radiological response, a confirmatory second scan at the next 6 week visit should be used to make these decisions. Please note that patients who have radiologically detected progressive disease only (even if confirmed at the second scan) do not need to stop trial treatment if it is felt that they may be receiving benefit from this.

Recommended acquisition parameters for 3T Philips model are listed below for reference. Please use parameters which are the equivalent on your model of scanner:

| IMAGE                                                                       | Orientation | Pulse parameters           |                      |                           | Flip Angle | Matrix  | FOV     | Slice gap (mm) | Slice thickness (mm) | No of acquisitions | TIME (min) |

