## 15.0 Quality Assurance

All MRI scans used to produce the outcome data for the final analysis will undergo a retrospective central review at the end of the trial as per [section 7.7](#), before analysis. Local treatment decisions will be based on local imaging results.

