#### AVF3708g and NCI 06-C-0064E studies

The AVF3708g study was a phase II trial in 167 patients (85 treated with single-agent bevacizumab) with glioblastoma at first or second relapse (Friedman, 2010). Of note only the efficacy data from the bevacizumab monotherapy arm (n=85) was used to support FDA drug approval. Findings were supported by the Phase II trial of bevacizumab in 48 patients with relapsed glioblastoma (Study NCI 06-C-0064E) (Kriesl, 2009).

- AVF3708g study - objective response rate was 28.2 % (95% CI: 18.5 -40.3%)
- AVF3708g study - median response duration was 5.6 months (95% CI: 3.0-5.8 months)
- AVF3708g study - the 6-month progression-free survival (PFS6) rate was 42.6% (97.5% CI: 29.6-55.5%)
- AVF3708g study - the 6-month PFS rates for patients at first and second relapse were 46.4% and 27.8% respectively
- AVF3708g study – the median PFS in first and second relapse was 4.4 and 3.1 months respectively
- AVF3708g study - the median overall survival was 9.2 months (95% CI: 8.2-10.7 months), median overall survival at first and second relapse was 9.1 months and 9.2 months respectively
- Study NCI 06-C-0064E - response rate was 35% percent by Macdonald criteria (one CR, 16 PRs)
- Study NCI 06-C-0064E – median PFS of 16 weeks (95% CI: 12-26 weeks)

Assuming a median PFS of 4 months with cediranib (as equivalent to bevacizumab) and an expected median PFS of 6 months on the combination cediranib plus gefitinib arm a total of 112 patients are required to achieve 110 events in order to detect a hazard ratio of about 0.67 between the two arms. This assumes an accrual period of 18 months, maximum follow up of 36 months,  $\lambda_1 = 0.115$ ,  $\lambda_2 = 0.1733$ , and a one sided type I error of 10% with approximate power of 80%. The sample size was generated using Nquery Version 7.0.

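### Imaging follow-up ends when a patient stops treatment for site-determined progression, but radiological PFS events are set only by central review after the trial, so unconfirmed patients have no sound PFS date

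*Protocol*

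**What the plan says.** **Who decides progression.** Protocol 2.6.1.1 has two routes to a PFS event short of death. Criteria 1 and 2 (clinical deterioration, or failure to return because of it) are judged by the site. Criteria 3 to 6, the radiological ones, are introduced with "As determined by retrospective radiographic central review". On timing, Section 7.7 says "The central review of MRI scans will be carried out retrospectively at the end of the trial". Section 15.0 adds: "Local treatment decisions will be based on local imaging results".

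**Who keeps being scanned.** Section 8.2 h: "If a patient discontinues due to progression, or has progressed after discontinuation, the patient will continue to be followed-up every 12 weeks for survival", by telephone. Section 13.1.2 says the same. The protection of 6-weekly imaging is worded for the other group: "For patients who are withdrawn from study treatment for reasons other than disease progression every effort will be made to continue with collecting the trial" (13.1.2, and likewise 8.2 f; the sentence goes on to name the imaging and its 6-week interval).

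**How PFS is closed.** Section 16.3 censors a patient with neither progression nor death at the last contact, not at the last scan. It also censors at the start of any medication likely to influence the endpoint.

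**Design.** Section 16.1 takes as control assumption "Assuming a median PFS of 4 months with cediranib (as equivalent to bevacizumab") and for the other arm an "expected median PFS of 6 months on the combination"; "a total of 112 patients are required to achieve 110 events", with a one-sided 10% type I error and about 80% power.

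**The concern.** While the trial runs, the only progression anyone can act on is the site's, because the central reading comes afterwards. The follow-up rule therefore depends on one assessor and the endpoint on another. When the two disagree, the scans that could have shown a later, centrally accepted progression were not required.

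The protocol itself expects disagreement. Section 7.7 warns that pseudoprogression is likely in these patients. Section 2.6.1.1 says that convincing non-enhancing growth may need one or two further scans. No rule states how a patient who is positive locally and negative centrally enters the primary analysis.

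The primary endpoint is at stake. Some patients would contribute survival time, or time to a telephone call, under the label of PFS. Others would be censored because someone suspected progression. A later analysis plan can change the rule but cannot recover scans never taken.

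**Working it through.** **1. The path through the text.** A patient stops for site-determined radiological progression, or progresses locally after stopping for another reason, and moves to 12-weekly telephone contact. Suppose central review then finds no progression on the scans up to that point, including any confirmatory or discontinuation MRI. Three outcomes remain:
- Site-assessed clinical deterioration qualifies under criteria 1 or 2. PFS has a valid event and there is no problem.
- No new therapy is recorded. PFS runs to death, or is censored at a telephone contact later than the last scan.
- New brain-tumour therapy starts (collected under 8.2 m). PFS is censored at that date under 16.3.

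**2. The design figure.** Schoenfeld, 1:1 allocation, HR = 4/6 = 0.667: events = 4(z₀.₉ + z₀.₈)²/(ln HR)² = 4(1.2816 + 0.8416)²/(0.4055)² = 110. Power with 110 events = 0.801. With uniform accrual over 18 months and cut-off 36 months after first entry, the mean event probability is 0.967, so 112 patients give 108.3 events. The stated 110 events and 112 patients are reproduced closely. They presume that the event is seen at progression.

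**3. PFS running on to death.** From the protocol: medians 4 and 6 months, 112 patients 1:1 (56 per arm), 18 and 36 months as above, one-sided 10% log-rank test. Assumed, because the protocol gives neither: a share f of patients locally progressed, off imaging and never centrally confirmed; and a further exponential time to death with median 5 months (Section 16.1 quotes a median overall survival of 9.2 months, about 5 beyond a 4-month PFS) or 3 months. Simulation used 4,000 trials per row.

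| f, both arms | Residual median | Medians, control / combination | HR | Power |
|---|---|---|---|---|
| 0 | none | 4.0 / 6.1 | 0.652 | 0.79 |
| 10% | 5 mo | 4.5 / 6.7 | 0.678 | 0.74 |
| 20% | 5 mo | 5.0 / 7.4 | 0.693 | 0.70 |
| 30% | 5 mo | 5.7 / 8.1 | 0.705 | 0.67 |
| 10% | 3 mo | 4.4 / 6.5 | 0.667 | 0.76 |
| 40% | 3 mo | 5.7 / 7.9 | 0.687 | 0.72 |

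The HR column is a one-step log-rank estimate. A separate run of 3,000 trials per row with Cox estimates and the 5-month residual gave HR 0.66, 0.68, 0.70, 0.72 and power 79%, 74%, 69%, 67% for f = 0, 10, 20, 30%. The two agree to within about 0.015 in HR.

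**4. Censoring at new therapy.** If the same patients are censored, with therapy taken to start at local progression, events fall to about 97, 87 and 76 and power to 0.76, 0.73 and 0.70 for f = 10, 20, 30%. Censoring at the moment of progression turns the event hazard λ into (1 − f)λ, so the Kaplan-Meier median becomes m/(1 − f). At f = 20% that is 4/0.8 = 5.0 and 6/0.8 = 7.5 months. The hazard ratio is unchanged only because f was set equal in both arms.

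**5. Unequal discordance, run-on to death, 5 months.** With 10% in the combination arm and 30% in control, HR is 0.84 and power 0.34. With 30% and 10%, HR is 0.57.

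**The case against.** A reader might infer that scans stop as soon as a site calls progression. The text does not say so. The trigger is discontinuation for progression, or progression after discontinuation. Treatment may continue after radiological progression (2.6.1.1, 7.1), and visits and scans then stay on schedule (8.2 k).

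A reader might also infer that every discordant patient's PFS becomes survival. That fails too: clinical deterioration counts without central review, and patients starting relevant medication are censored at its start.

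The protocol already has safeguards. Section 13.1 asks for a second scan 6 weeks later before withdrawal on radiology alone. Sections 7.7 and 8.2 f ask for a discontinuation MRI within 10 days where possible. Such images go to central review, and it does not matter that they are read late. This reduces discordance but does not remove it. The second scan is advice tied to treatment decisions, so it does not reach a patient who progresses locally after already stopping. Central review may also decline to confirm on both scans.

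The schedule in 8.1 marks MRI and Karnofsky status under long-term follow-up, and 8.2 h continues neurological assessments. That column covers both the 6-weekly and the 12-weekly group without saying which the marks concern. It conflicts with telephone-only follow-up rather than settling it.

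The size rests on assumptions, and this criticism stands. The discordance rate and residual survival are not in the protocol, and a difference of two medians is not a post-progression survival figure. The model also takes the local call as the true progression date. If it was pseudoprogression, part of the longer PFS is genuine.

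**Conclusion.** The point holds in a limited form. For patients who leave imaging because of site-determined radiological progression that central review does not confirm, and who have no qualifying clinical deterioration, the protocol yields either a PFS time reaching past the last scan or a probably informative censoring.

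With 10–30% discordance, equal in both arms and all running to death with a 5-month residual, power falls from about 79% to 74–67% and the hazard ratio moves from about 0.66 to 0.68–0.71. With a 3-month residual, power is 0.76 to 0.72 over 10–40%. These figures show sensitivity and are not predictions. They overstate the loss to the extent that patients leave by the clinical route. Equal discordance mainly attenuates the effect; unequal discordance biases it in either direction. The sample size calculation is not in error.

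**What to change.** **Sections 8.2 h and 13.1.2.** Make the change to 12-weekly telephone follow-up after local radiological progression conditional on the second 6-week scan, already called for in 2.6.1.1 and 13.1, having been acquired and submitted for central review. This governs data collection only and leaves treatment decisions as they are. Reconcile the long-term column of the 8.1 schedule and 8.2 f with it, stating which patients have MRI and Karnofsky assessments after discontinuation.

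**Section 16.3.** For patients whose imaging stopped after a local call and who have no centrally confirmed radiological progression, state that a survival telephone contact does not extend PFS. Prespecify one rule, for example censoring at the last evaluable scan or assessment. Counting the local progression date as an event is the alternative. Add a supporting PFS analysis on local assessment, here or in the analysis plan; sites already report progression locally.

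**Cost.** A few sentences, one extra analysis, and some effort to secure a scan mostly advised already. For patients who progress locally after stopping for another reason, it may be one further scan. Neither rule is free: the first keeps some informative censoring, and the second counts some over-called progressions as events. The supporting analysis shows how much the choice matters.
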